**Patients Ineligible for Intervention after 4 weeks of TB Treatment**

Patients who have persistent contraindications to starting ARV therapy after 4 weeks in Step 1 will remain in the study. Patients in this group are followed because of our ethical obligation to them after enrolling them in the study. These patients will be treated for active tuberculosis and monitored for primary study outcomes according to the schedule for assessments outlined in Step 2. These patients will be registered to Step 2 but will not be randomized nor will they be included in the primary analysis of the study. They will be eligible for entry into Step 3 of the study if, during the study period, their CD4 count drops below 250/ml or an AIDS- defining condition develops as defined by WHO stage IV HIV infections or a definitive diagnosis of a severe bacterial infection that meets WHO Stage 3 classification (Appendix II)

#### **5.2.1.2 Drug Formulations and Doses**

Trizivir®

Abacavir 300 mg/lamivudine 150 mg/zidovudine 300 mg (ABC/3TC/ZDV, Trizivir™) will be administered orally BID with or without food. Store at 25 (77 F); excursions permitted to 15-30C (59-86F).

Combivir®

Lamivudine 150-mg/zidovudine 300-mg combination tablets (3TC/ZDV, Combivir®) will be administered orally BID, with or without food. Store at 25 (77); excursions permitted to 15-30C (59-86F).

EPIVIR®

Lamivudine (3TC) 150-mg and 300-mg tablets (EPIVIR®) will be administered orally as 150 mg BID with or without food. 300 mg tablets are available for once a day, nighttime dosing. Store at 25°C (77°F), excursions permitted to 15°-30°C (59°-86°F).

RETROVIR®

Zidovudine (ZDV) 300-mg tablets (RETROVIR®) will be administered 300 mg BID with or without food. 100-mg capsules are available for dose reduction. Store at 15° to 25°C (59°-77°F) and protect from moisture.

ZIAGEN®

Abacavir sulfate (ABC) 300-mg tablets (ZIAGEN®) will be available as single agent and administered at a dose of 600 mg QD, with or without food. Store at controlled room temperature of 20° to 25°C (68°-77°F)

Sustiva®/ or Stocrin™

Efavirenz (EFV) 200-mg capsules (Sustiva® or Stocrin™): Store at 25°C (77°F); excursions permitted to15-30C (59-86F). EFV 600 mg will be administered orally QD, on an empty stomach (i.e., 1 hour before or 2 hour after a meal), unless the patient is taking rifampin concurrently when 800 mg will be given. Bedtime dosing may improve tolerability of nervous system symptoms. During punctuated therapy, the dose will be given during the day as modified directly observed therapy. For those on punctuated therapy who experience CNS side effects, EFV may be administered at bedtime. For patients taking rifampin, dose reduction from 800-mg to 600 mg QD EFV is allowed if CNS symptoms persist.Women of reproductive potential if participating in activity that could lead to pregnancy must use two reliable methods of contraception while receiving Efavirenz and for 6 weeks after Efavirenz is discontinued.

Viramune® Nevirapine (NVP) 200-mg tablets: Store at room temperature, 15°-30°C(59°-86°F). NVP 200 mg will be administered orally QD for the first 2 weeks (lead-in), then 200 mg orally BID thereafter. The designated health care provider should review the signs and symptoms of NVP-related hypersensitivity and hepatitis with the subject prior to dispensing NVP. Subjects should contact their medical officer if they develop rash, or signs and symptoms of hypersensitivity or hepatitis. If rash occurs during the lead-in, do not escalate the dose until the rash has resolved. After reaching full dose, if NVP dosing is interrupted for >7 days NVP should be started with the lead-in of 200 mg orally QD for 2 weeks, then 200 mg orally BID. NVP may be taken with or without food.

**Table 5. Standard Starting Doses and Dose Reductions for Antiretroviral Therapy**

| DRUG | INITIAL DOSE | DAILY DOSE | REDUCED DOSE | DAILY REDUCED DOSE |
| --- | --- | --- | --- | --- |
| EFV | 600 mg QD | 600 mg | No Reduction | No Reduction |
| EFV1 | 800 mg QD | 800 mg | 600 mg QD | 600 mg |
| ZDV | 300 mg BID | 600 mg | 200 mg BID | 400 mg |
| 3TC | 150 mg BID | 300 mg | No Reduction | No Reduction |
| ABC | 300 mg BID | 600 mg | No Reduction | No Reduction |
| NVP | 200 mg QD x 14 d, then 200 mg BID | 200 mg x 14 d, then 400 mg | No Reduction | No Reduction |

**1 While receiving rifampin**

#### **5.2.1.3 Antiretroviral Drug Supply, Distribution, and Pharmacy**

ABC/3TC/ZDV (as Trizivir®), 3TC/ZDV (as Combivir®), ABC (as Ziagen®), 3TC (as Epivir®), and ZDV (as Retrovir®) will be provided by GlaxoSmithKline. EFV (as Sustiva or Stochrin) will be purchased locally from the Joint Clinical research Center with institutional funds. Nevirapine (as Viramune®) will be purchased locally from the Joint Clinical research Center with institutional funds.

##### 5.2.1.3.1 Pharmacy

The antiretroviral study medications will be shipped to and stored at the pharmacy at the Joint Clinical Research Center (JCRC) in Kampala, Uganda. The JCRC has extensive experience in procuring, storing, and dispensing antiretroviral medications. The JCRC pharmacy is staffed by trained pharmacists with experience in dispensing antiretroviral medications.

This pharmacy will be responsible for maintaining an inventory of study medication, ensuring proper storage, and producing timely reports of medication use. The pharmacist will be responsible for packaging antiretroviral therapy in packets with labels for individual study patients. These packets will be given to study home visitors for directly observed therapy. Empty packets will be returned to the pharmacy.

#### **5.2.1.4 Anti-retroviral Drug Substitutions and Replacements**

If a patient develops intolerance to Trizivir® at any point in the study or fails to achieve viral suppression on therapy (Section 8.1.3), then an alternative regimen will be selected by study physicians based on the type of intolerance observed, the causative agent, and availability of medication. Single drug formulations of abacavir, lamivudine, and zidovudine will be available for dose adjustments of combination ABC/3TC/ZDV (as Trizivir®) as clinically indicated. Efavirenz and 3TC/ZDV (as Combivir®) will be available to substitute for ABC/3TC/ZDV (Trizivir) when abacavir-related HSR or intolerance occurs. Efavirenz will be substituted for ZDV or 3TC when dose limiting toxicity occurs to these medications. Nevirapine will be available for substitutions of efavirenz for treatment-limiting toxicity and substitution of efavirenz during pregnancy as clinically indicated. Nevirapine cannot be substituted for efavirenz or any component of Trizivir in the following circumstances: women with CD4>250 OR men with CD4>400 at the time of proposed NVP initiation. See section 5.2.1.2 for formulations and initial dosing.

If a patient develops intolerance to ABC during punctuated therapy, he/she will receive efavirenz (800 mg) + ZDV (300 mg) + 3TC (150 mg) BID. Efavirenz (EFV) will be administered at a dose of 800 mg when patient is receiving rifampin because of the drug interaction between EFV and rifampin. Efavirenz otherwise will be administered at a dose of 600 mg. EFV will be given with modified directly observed therapy, usually during the day.

Options for third-line study drugs will be at the study physician’s discretion. Alternate choices will be made based on drug availability, cost, participants prior ARV drug experience, and the study physician’s clinical judgment.

These drugs are currently available in Uganda through the Joint Clinical Research Center and will be purchased on a case-by-case basis.

### **5.2.2 Randomization**

Treatment intervention will be randomly allocated to patients with active TB when patients enter Step 2 of the study. Eligible TB patients will be randomized with an allocation ratio of 1:1 to receive either punctuated ARV therapy or anti-TB treatment only with delayed ARV therapy. Randomization will be done with a permuted-block size of 16 to reduce the likelihood of unbalanced study arms in terms of size and prognostic factors. The assignment to study arm will be made by the UCSF data center to reduce the likelihood of inappropriate enrollment or treatment allocation.

Before the trial begins a list of computer-based random numbers will be generated using a pseudo-random number generator. These randomly allocated numbers will be used to assign eligible study patients to study arm. This list will be retained at the data center at UCSF. Once eligibility for study entry into Step 1 has been determined through the screening process, a form that contains a summary of study entry inclusion and exclusion criteria will be sent to the statistical center. Patients enter Step 1 where they are started on anti-TB treatment and monitored for contraindications to start the Trizivir-based ARV intervention regimen. All patients will be assessed beginning at week 1 and up to week 3 for contraindications to starting intervention. Upon determination of eligibility criteria for randomization, a form with criteria for randomization will be sent to the UCSF data center. Study entry and randomization criteria will be verified and a treatment assignment made according to the list of random numbers. Upon randomization, patients enter Step 2 of the study where they are initiated into study arm. Patients with contraindications for starting Trizivir-based punctuated ARV therapy without resolution during the 2 to 4 week period will be registered to Step 2, will not be randomized, will not be included in the primary analysis of the study, but will remain on study follow-up. They will be eligible for entry into Step 3 of the study, if during the study period, their CD4+ count drops 250/ml or an AIDS- defining condition develops as defined by WHO stage IV HIV infections or a definitive diagnosis of a severe bacterial infection that meets WHO Stage 3 classification (Appendix II).

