**5.0 STUDY PHASES: STUDY ENTRY, INTERVENTION AND POST-OUTCOME**

##

## 5.1 Study Entry – Step 1

All patients in this study will receive routine treatment for tuberculosis (see Section 5.1.1). The experimental intervention in this study is the use of punctuated antiretroviral therapy for six months during treatment for tuberculosis. Because standard anti-TB drugs represent the background treatment, these drugs will not be considered study drugs. When patients have been found to be eligible for the study and have given informed consent, all patients will be started on antituberculosis treatment, given daily for a total of six months and will have the following baseline assessment:

1. Informed consent for study
2. Medical history and physical examination, including weight
3. HIV RNA Roche Amplicor
4. PBMC storage/ immune function (Flow cytometry to assess cell surface activation markers, EliSpot to assess CD4 and CD8 T cell specificity to HIV and microbial peptides, Whole blood assays to determine antigen specific response to HIV and microbial antigens)
5. Plasma & Buffy Coat storage

Patients will be evaluated weekly while in Step 1. At one week from study entry all patients will be assessed for readiness to start on the Trizivir-based punctuated ARV therapy with the following evaluation:

1. Medical history and physical examination, including weight
2. New Diagnosis and hospitalization survey
3. Adverse event survey
4. Pregnancy test (urine or serum *β*-HCG)
5. Complete blood count with differential
6. Liver function tests (AST and serum bilirubin)
7. Serum creatinine
8. Adherence to antituberculosis therapy
9. Quality of life survey
10. Disease specific diagnostic tests

The patient will be scheduled to return to the clinic 1 week after this evaluation (two weeks after the start of TB therapy) to be randomized or identified as having contraindications (see Section 4.4). If the patient has contraindications to starting the Trizivir-based ARV intervention they will be scheduled to return to the clinic in another week (Week 3) and be reassessed.

Thus, all patients evaluated at week 1 will be scheduled to return to the clinic at week 2, and may be randomized or reassessed for randomization at that time; those patients that have contraindications at week 2 may be scheduled to return to the clinic for randomized or reassessment at week 3; and those patients reassessed at week 3 will be scheduled to return to the clinic and may be randomized at week 4.

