### **5.2.3 Blinding**

The ARV intervention will be open-label. In the proposed design, study subjects and physicians alike will be aware of the treatment assignment at the initiation of the intervention. The initiation of the intervention will occur between 2, and 4 weeks following initiation of standard anti-TB treatment. A placebo controlled design was not chosen because of ethical concerns and the sensitivities regarding placebo trials in the study population.

To address detection and reporting bias, we will use a reproducible, laboratory-based endpoint based on CD4+ measurements that is not subject to interpretation by investigators or subjects. Laboratory specimens will be identified by study subject ID numbers. Laboratory staff performing safety, microbiological and immunologic assays will be blinded to treatment arm assignment. Clinicians will be masked to treatment assignment during chest X-ray reading.

To minimize bias further, the frequency and duration of follow-up will be similar in both study arms. Outcome data will be collected and recorded in a standard manner for all study subjects. A Clinical Review Committee composed of senior level faculty at Case Western Reserve University, University California San Francisco, Makerere University review and classify all study outcomes (Table 6) in a blinded manner. Losses to follow-up will be recorded; reasons for the loss to follow-up will also be recorded. The potential bias from unbalanced treatments of intercurrent infections will be minimized by the use of a standard protocol for the treatment of these conditions.

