# 10.0 STATISTICAL CONSIDERATIONS

## 10.1 Sample Size

In this randomized clinical trial we will enroll a total sample size of 350 HIV-infected TB patients into Step 2 with 175 randomized to punctuated therapy and 175 randomized to anti-TB treatment only and delayed ARV therapy. The sample size was estimated to provide a power of 80 – 90% to detect an effect size of 35% or greater for HIV disease progression. This effect size translates into an average delay of about one year before the need to start ARV therapy. The sample size will not include patients who enter Step 1 but are not eligible to progress to Step 2.

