The primary outcome for the study is HIV disease progression. This is defined as the time interval between enrollment and the development of one or more of the following endpoints, whichever occurs first: decline of CD4+ count < 250/µL, new AIDS-defining condition, or death. When a subject has met the criteria for primary outcome for CD4+ counts, the date for the first of 2 consecutive CD4+ counts will be used to mark failure time. The primary analysis of the study for each outcome will be to compare the failure-time distribution of the treated to the reference group. Separate failure-time distributions will be estimated for each treatment group using the Kaplan-Meier method78 and compared using the log-rank test.79 Stratified analysis will be performed for the primary outcome according to categories of baseline viral load.80 A Cox proportional hazards regression model81,82 will be developed to evaluate the effect of treatment on disease progression. In these analyses, the failure event will be HIV disease progression; subjects will be censored because of withdrawal during the study or at end of study. We will assess whether censoring is independent of study outcome as this is a fundamental assumption of survival analysis. In these regression models, observed event-free survival will be the dependent variable.

The basic Cox proportional hazards model for this analysis will be formulated as follows:

where h (t,X) is the observed hazard, h0 (t) is the baseline, unmeasured hazard for disease progression, β is the regression coefficient for treatment, ARV is the variable coding for immediate versus delayed ARV treatment (1 and 0, respectively), i the vector of regression coefficients for the covariates, Xi is the vector of covariates that may include time since treatment. This vector will contain known prognostic factors for HIV infection in Africa such as age, tuberculin skin test, baseline CD4+ count, hemoglobin, and performance status. This vector of covariates will also include the time period between initiating antituberculosis therapy and date of randomization to account for varying times in initiating antiretroviral therapy. The assumption of proportional hazards will be tested using graphical methods and formal statistical tests. If this assumption does not hold, then stratified Cox regression models will be developed, stratifying on the variable with non-proportional hazards.

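### The protocol prints one fixed, unstratified block size of 16 for an open-label, single-center trial, so up to about 11% of assignments could be known in advance (minor)

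*Protocol*

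**What the plan says.** Section 5.2.2 sets the scheme: "Eligible TB patients will be randomized with an allocation ratio of 1:1", and "Randomization will be done with a permuted-block size of 16 to reduce the likelihood of unbalanced study arms in terms of size and prognostic factors". It names no stratification factor. The UCSF data center keeps the list, and on receipt of the site's form, "Study entry and randomization criteria will be verified and a treatment assignment made according to the list of random numbers". Viral load enters as a stratum only at analysis (section 10.2.2.1): "Stratified analysis will be performed for the primary outcome according to categories of baseline viral load". The number to be randomized is in section 10.1: "we will enroll a total sample size of 350 HIV-infected TB patients into Step 2".

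Treatment is not masked. Section 5.2.3 says "study subjects and physicians alike will be aware of the treatment assignment at the initiation of the intervention". Section 9.1 names one Clinical Center.

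The date of randomization can move. Patients are assessed at week 1 for randomization at week 2. Under section 5.1, "those patients that have contraindications at week 2 may be scheduled to return to the clinic for randomized or reassessment at week 3", with a last opportunity at week 4. Section 4.4 lists the conditions that block randomization. Patients not randomized by week 4 stay in follow-up but are left out of the primary analysis (sections 5.2.1.1 and 5.2.2).

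**The concern.** With one list, one clinic, visible assignments and a block size printed in the protocol, anyone at the site who keeps a tally can count down each block. Keeping the list in San Francisco conceals the list, not what can be worked out from earlier assignments plus a known block size. Section 5.2.3 describes measures against detection and reporting bias; it has none against selection at allocation.

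Prediction matters only if someone can act on it. Site staff carry out the weekly assessments, which include fever and weight, and decide when the randomization form goes to UCSF. Screening CD4+, which bears directly on the primary endpoint, is known by then. If entry were timed so that patients with better or worse prognosis met a predicted arm, the arms would differ at baseline and the unadjusted log-rank comparison would be biased. A patient held past week 4 would leave the primary analysis altogether, which introduces bias if the delay depends on the predicted arm.

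**Working it through.** The protocol gives no predictability figure, so there is nothing to reproduce first.

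**Inputs.** Block of 16 at 1:1, so m = 8 per arm (5.2.2); 350 randomized (10.1). For the error calculation, from section 10.1 and the legend to Figure 5: reference median 2 years, 3-year accrual, 5% dropout per year, two-sided alpha 0.05. The total duration of 5 years is in the synopsis. The observer is assumed to know the block size and where blocks start, and to see every assignment.

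**Certain assignments.** The expected number per block is 2m/(m+1) = 16/9 = 1.78, and 1.78/16 = 11.1%. Since 350 = 21 × 16 + 14, the last block stops two short. Position 16 is always certain; position 15 is certain with probability 2 × (8/16) × (7/15) = 0.467. The partial block therefore adds 1.778 - 1 - 0.467 = 0.311, and the total is 21 × 1.778 + 0.311 = 37.6, about 38 of 350 (10.8%).

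**Correct guesses.** Guessing the arm with more places left gives, per block, m + (4^m / C(2m,m) - 1)/2 = 8 + (65,536/12,870 - 1)/2 = 10.05, and 10.05/16 = 62.8%. Over 350 patients this is about 219, or 44 more than the 175 expected by chance.

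**Other block sizes, same formulas.**

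| Fixed, known block | Certain | Correct guesses |
|---|---|---|
| 4 | 33.3% | 70.8% |
| 8 | 20.0% | 66.6% |
| 16 | 11.1% | 62.8% |
| 20 | 9.1% | 61.7% |

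**Type I error if guesses are acted on.** Suppose there is no treatment effect, and that patients entered against a guess of one arm differ in hazard from those entered against a guess of the other by a ratio R (assumed). The log hazard ratio between arms is then about ln(R) × (2 × 0.628 - 1) = 0.256 × ln(R). With hazard ln2/2 and dropout hazard 0.0513, the expected event fraction is 0.642, giving 0.642 × 350 = 224.6 events and a shift in the log-rank z of |log HR| × sqrt(224.6)/2 = 7.49 × |log HR|.

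- All patients steered, R = 0.7: null HR 0.91, shift 0.68, error 10.5%.
- All patients steered, R = 0.5: null HR 0.84, shift 1.33, error 26.4%.
- 20% steerable (assumed): shifts of 0.14 and 0.27, errors 5.2% and 5.8%.

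Null log-rank simulations agree: about 10-11% and 23-27% under full steering, and about 5-6% with 20% steerable. Acting only on the certain assignments gives about 6% (R = 0.7) and 8-9% (R = 0.5).

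**Alternatives.** Undisclosed random block sizes from 12 to 24 leave the guess rate at about 62%, and the full-steering errors at 9.7% and 22.2%. A big-stick rule (a fair coin toss, with a forced assignment when the imbalance reaches a cap b) has a long-run correct-guess rate of 1/2 + 1/(4b). With b = 8 this is 53.1%, and full-steering error is about 5-6%. Its forced share is 1/(2b) = 6.3%, which is predictable only if the cap is known.

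**The case against.** The strongest reply is that the scheme leaves little room to steer.

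- **Timing.** Week 2 is the default. Later randomization needs a listed contraindication; most are laboratory values, laboratory staff are blinded (5.2.3), and UCSF checks the criteria before assigning. A reader might infer that staff may defer at will, but sections 3.2 and 4.4 do not allow that. What remains is the site's own clinical assessment and its timing of the form.
- **Lag.** At the projected 3 patients per week (4.5), a one-week deferral means about three assignments not yet seen. With the last three unseen, simulated guess accuracy falls to 56.7% and the error to 6.0% (R = 0.7) or 9.7% (R = 0.5), even with every patient steered.
- **Adjustment.** The planned Cox model includes baseline CD4+, hemoglobin, performance status and the time from TB treatment to randomization, and section 10.2.1 compares baseline characteristics. Stratifying on the steered factor brought the simulated full-steering error back to 5.6% (R = 0.7) and 4.1% (R = 0.5). That protects the adjusted analysis against measured factors; it does not protect the log-rank comparison.
- **Cause.** A reader might blame the whole 63% on disclosure. Only the certain 11% comes from a fixed, known size; undisclosed large blocks are guessed nearly as well. Sixteen is already a fairly large block.
- **Rationale.** It is tempting to call the prognostic-balance claim wrong. That is too strong: the text speaks only of reducing likelihood, and blocking does limit imbalance in factors that drift over a three-year accrual. The wording is loose.

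These points stand and reduce the size of the problem. None of them justifies printing the block size.

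**Conclusion.** The point holds as a minor design weakness. The 11% and 63% are exact for an observer who follows every assignment and knows the block starts. One list, one clinic and open treatment make that feasible, but the figures are upper bounds and not a forecast of conduct. A reader might infer that the trial's type I error is 11% or 27%. The documents do not support this, because those values need every patient steered to the next place at assumed hazard ratios of 0.7 or 0.5. With about 20% steerable, also an assumption, the error is about 5-6%, close to nominal. The case for change is that the exposure can be removed at almost no cost.

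**What to change.** In section 5.2.2, delete the block size. State that UCSF generates and holds the allocation method in a restricted document not available to the clinic, using randomly varying large block sizes (for example 12 to 24). This removes nearly all certain assignments and leaves the guess rate at about 62%.

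Optionally, use a big-stick rule with a withheld cap (for example 8), which lowers correct guesses to about 53%. The final arm sizes could then differ by up to 8 of 350, with negligible loss of power.

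Do not move to smaller blocks, which are easier to predict. Reword the rationale to say that blocking keeps arm sizes balanced over time.

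The cost is one edited paragraph and a regenerated list at UCSF, with no added visits or staff.
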